Therefore, informed by the Rome Foundation Consensus Statement on the design of BGBT clinical trials [47], the ORBIT (Obesity-Related Behavioral Intervention Trials) model of behavioral treatment development for chronic diseases [48], and the National Institutes of Health (NIH) stage model for behavioral intervention development [49], and building on prior qualitative research [50] and a systematic review [14], we developed the WISH (Well-being in IBS: Strengths and Happiness) program, a novel, 9-week, manualized, phone-delivered PP intervention specifically adapted to IBS. We examined its feasibility, acceptability, and potential effects on key clinical outcomes in a prior proof-of-concept randomized waitlist-controlled trial (N=22) [35]. WISH was found to be preliminarily feasible (85% of all sessions were completed, exceeding our a priori threshold of 67%), easy to complete (mean 7.2 out of 10, 95% CI 6.70-7.75), and subjectively helpful (mean 7.6 out of 10, 95% CI 7.14-8.01). Promising signals for improvement on several clinically meaningful outcomes, including IBS symptom severity, IBS health-related quality of life, resilience, GI symptom-specific anxiety, restrictive and avoidant eating, perceived stress, and pain catastrophizing, were identified, with effect sizes (Cohen *d*) ranging from 0.1 to 0.7. Of particular note, 61% (11/18) of participants no longer met Rome IV criteria [51] for IBS after intervention completion. Though this proof-of-concept trial provided promising initial data regarding WISH, it had a small sample, no active control condition, no extended follow-up to assess sustainability of effects, and no examination of potential underlying gut-brain mechanisms, the latter of which is often missing from BGBT clinical trials. Additionally, participant feedback highlighted areas for further refinement, including greater customization of intervention content to IBS and expanded descriptions of connections between PP exercises and the gut-brain axis.

Accordingly, we now seek to evaluate the feasibility, acceptability, preliminary effects, and candidate gut-brain mechanisms of an optimized and refined version of WISH (WISH 2.0) in a randomized controlled trial (RCT; N=50) compared with a time- and attention-matched educational control.

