### Assessment Visits

Participants complete 4 assessments: baseline (in-person), intervention midpoint (remote), the postintervention assessment (in-person), and the 3-month postintervention assessment (remote). Written informed consent is obtained electronically via a secure REDCap platform at the baseline visit. At each assessment, participants complete a set of self-report questionnaires electronically via a secure REDCap link. In-person assessments are conducted at the hospital’s Translational and Clinical Research Center. At the 2 in-person visits (ie, at baseline and immediately after the intervention), participants also provide a blood sample for whole transcriptome and serum inflammatory biomarker analyses and undergo HRV assessment with the emWave Pro Plus (HeartMath Institute), a validated photoplethysmography ear-clip sensor [64,65]. HRV is measured for a total of 9 minutes while participants complete a set of standardized tasks (5 min of resting at baseline, 3 min of focused attention, and 1 min of deep breathing). Additionally, participants complete a brief exit interview as part of the postintervention assessment.

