### Analytical Approach

#### Power and Sample Size

This pilot trial (N=50) is powered to evaluate feasibility and acceptability and is not designed to detect statistically significant between-group differences in exploratory clinical or mechanistic outcomes. Based on our prior proof-of-concept trial [35], with 25 participants in the PP intervention, we will have 90% power to detect a difference between our expected proportion of 80% of participants completing at least 6 (67%) of 9 PP activities and the null hypothesis (true proportion of 50% or less) at the 2-sided .05 significance level using a proportion test (power oneproportion routine in Stata version 17; StataCorp LLC). Similarly, for acceptability, assuming the same mean ratings as in our prior proof-of-concept trial [35] and an average of 6 measurements from the 25 PP intervention participants, this study has more than 90% power to detect a mean acceptability rating of ≥7.0 of 10 (simulation-based power calculation). Regarding the exploratory mediation analyses, with our sample size of 50 participants, we will have 81% power to detect a mediation effect of at least 0.44 assuming a standardized mediator with SD of 1, a standardized outcome, and a correlation between the treatment and the mediator of 0.4 at the 2-sided .05 significance level (powerMediation.VSMc command from the *powerMediation* library in R; R Foundation for Statistical Computing). Although we do not anticipate finding significant mediation effects in this pilot trial, these analyses may help identify promising candidate gut-brain mechanisms that merit examination in a future, larger randomized efficacy trial.

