#### Statistical Analysis Plan

Feasibility will be assessed using proportions and exact binomial CIs. Acceptability will be evaluated using a random-effects model with a participant-specific random effect to account for within-participant correlation among ratings. This model will also facilitate estimation of the between- and within-participant variance of the ratings. Qualitative exit interviews will be coded by 2 independent coders with a goal of interrater reliability >0.80. Discrepancies will be resolved by consensus, and themes will be derived from iterative review of coded data. To assess the immediate impact of the respective exercises on happiness, optimism, and IBS knowledge, 2-tailed paired *t* tests will be used. Between-group differences in the proportion who achieve the MCID (≥50-point reduction in the IBS-SSS) will be evaluated using logistic regression. Achieving the MCID (yes or no) will be modeled as the dependent variable, with treatment group (WISH 2.0 vs educational control) included as the primary independent variable. For clinical outcomes that are measured multiple times per participant, preliminary effects will be explored using mixed-effects regression models with fixed effects for a categorical effect of time and a time-by-treatment interaction with a common baseline for the 2 groups, and an unstructured covariance matrix for the residuals to account for repeated measures. The time-by-treatment interaction terms will estimate the difference between groups in the change over time. Because the mixed-effects model uses maximum likelihood to estimate the coefficients, this approach is valid when missing data are missing at random. Effect sizes (modified Cohen *d*) will be calculated by dividing the group×time coefficient by the SD of the difference estimated using the appropriate variance components from the unstructured covariance matrix. Exploratory mechanistic analyses will use linear mixed models to assess changes in candidate gut-brain mechanisms (eg, HRV, interoception, gene expression, and immune activity) in response to the intervention. If there are skewed distributions in the candidate mechanistic data, logarithmic transformations will be applied. Given the exploratory nature of these analyses, no correction for multiple comparisons will be used. In addition to the models that examine each outcome separately, we will also preliminarily explore whether these gut-brain mechanisms might mediate IBS symptom change using a mediation model. We will calculate the change in the candidate mechanism measurements using linear regression for each participant and the change in the clinical effects outcome measures. Then, we will fit a mediation model with the change in the clinical effects outcome measures as the outcome, the change in the mechanistic measurements as the mediator, and the treatment group as the predictor. The direct and indirect effects of the treatment on the clinical effects outcome measures will be estimated from this approach. Finally, the mediation effects will also be estimated by calculating the change in the treatment effect from the linear mixed model used to assess preliminary clinical effects and the treatment effect from a linear mixed model including treatment, time, time-by-treatment interaction, baseline mechanistic data, and change in mechanistic data as the predictors. The change will show the indirect effect through changes in candidate gut-brain mechanisms. All analyses will be conducted using Stata (version 17). Analyses of clinical and candidate mechanistic outcomes will be conducted on the intention-to-treat population (all randomized participants), with sensitivity analyses using the per-protocol population where appropriate.

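### The difference-in-treatment-effect mediation estimate would compare models fitted to different participants for HRV and blood markers, so the difference is not purely an indirect effect

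*Protocol article*

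**What the plan says.** The Statistical Analysis Plan section gives two mediation approaches. The first regresses change in outcome on treatment and change in mechanism. The second is obtained by "calculating the change in the treatment effect from the linear mixed model used to assess preliminary clinical effects" and comparing it with the effect from "a linear mixed model including treatment, time, time-by-treatment interaction, baseline mechanistic data, and change in mechanistic data as the predictors". The reading given to the result is unqualified: "The change will show the indirect effect through changes in candidate gut-brain mechanisms".

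Three other statements bear on it:

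- Missing data for the clinical model: "Because the mixed-effects model uses maximum likelihood to estimate the coefficients, this approach is valid when missing data are missing at random".
- Population: "Analyses of clinical and candidate mechanistic outcomes will be conducted on the intention-to-treat population (all randomized participants").
- Collection, under Assessment Visits: "At the 2 in-person visits (ie, at baseline and immediately after the intervention), participants also provide a blood sample". HRV is recorded at the same two visits. Questionnaires are completed through an electronic link at all four assessments. Table 3 agrees, and shows MAIA-2 also at week 5 and at extended follow-up.

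The Power and Sample Size section bases its mediation figure on everyone randomized: "Regarding the exploratory mediation analyses, with our sample size of 50 participants", giving 81%.

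**The concern.** A difference between two treatment effects measures an indirect effect only if the mechanism adjustment is the one thing that changes between the models. Here the set of participants can change as well. The maximum-likelihood argument covers missing outcomes. It does not keep a record whose covariate is missing, and in the second model the mechanism change is a covariate. Someone who answers questionnaires but lacks the second HRV or blood measurement counts in the first model and drops out of the second, unless the covariate is imputed.

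The difference then contains a component that would be present even if the mechanism had no effect on outcome. The article says these analyses may identify mechanisms worth testing in a larger trial, so the risk is a misleading ranking of candidates. No primary conclusion is at risk.

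**Working it through.** **1. The plan's own figure.** Inputs from Power and Sample Size: n=50, effect 0.44, treatment-mediator correlation 0.4, SDs of 1, two-sided 0.05. The formula behind the cited routine is power = Φ(0.44 × √n × √(1 − 0.4²) − 1.96).

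- n=50: 0.44 × 7.071 × 0.9165 = 2.85, so Φ(0.89) = 0.81. The stated 81% is reproduced.
- n=45 (10% without a change score): 77%.
- n=40 (20%): 72%.

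For scale, with 1:1 allocation a correlation of 0.4 is a mediator difference of 0.4/0.5 = 0.8 SD. The implied indirect effect is 0.8 × 0.44 = 0.35 SD.

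**2. Who is in each model.** Clinical model: everyone with usable questionnaire data. Mechanism-adjusted model: those with baseline and postintervention values of that mechanism. For HRV, RNA and serum markers the second set excludes anyone who missed the second in-person visit. A MAIA-2 slope can usually still be formed from other time points.

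**3. Random loss, all questionnaires kept.** The article gives no rate of missed visits, so 10-20% is an assumption. To isolate the change of sample, take the same unadjusted model on everyone minus on those with a change score. With correlation ρ=0.5 to baseline, the variance of the postintervention effect is about 4(1 − ρ²)/n. The variance of the difference between full set and subset is about 4(1 − ρ²)(1/n − 1/50) = 3(1/n − 0.02).

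- n=45: √0.0067 = 0.08.
- n=41: √0.0132 = 0.11.
- n=40: √0.0150 = 0.12.

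Simulation (N=50, four visits, exchangeable correlation 0.5, true effect 0.4 SD, no mediation) gave 0.086, 0.118 and 0.122-0.127 at 10, 18 and 20% missing. All are centred on zero.

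**4. Random loss, postintervention questionnaire also lost.** The first model now keeps these people only through their other assessments. In the same simulation at 18% missing, the SD falls to 0.047 (follow-up kept) or 0.038 (only baseline and midpoint kept). A second set-up (unstructured covariance, true effect 0.5 SD, mechanism unrelated to outcome) gave 0.04 and 0.06 at 10 and 20%, and 0.08 at 20% with another assumed correlation matrix.

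**5. Non-random loss.** If loss depends on midpoint symptoms equally in both arms, the mean shift is about 0.01. If WISH 2.0 non-responders selectively miss the visit, the first set-up gave 0.03-0.08 over 10-20% missing; a repeat run gave 0.03-0.04 at 18%. The second set-up, across different arm-dependent patterns, gave 0.05-0.17 at 20%.

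**6. Is a common set enough?** It makes the sample component exactly zero, but two features of the second model as listed remain. It has a treatment main effect, which the clinical model's common baseline omits. The mechanism enters only as a time-constant main effect.

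- With complete data and no baseline constraint in either model, adding the time-constant mechanism terms left every time-by-treatment coefficient unchanged.
- With a true indirect effect of −0.26 SD, the listed subtraction returned −0.01. Mechanism-change-by-time terms with a common baseline in both models returned −0.27.
- With complete data and no mediation at N=50, the listed difference still had an SD of 0.14.

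**The case against.** The strongest reply is that the article never says complete cases. The mismatch follows from how mixed models treat a missing covariate, and an unseen analysis plan might impute or fix a common set. This stands as a limit on the claim, which is therefore conditional on no imputation. It does not remove the point: the article fixes the estimator, takes its first term from the main clinical model, interprets the difference without qualification and claims all randomized participants.

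A reader might infer that about 18% will lack a mechanism change, because the proof-of-concept trial had N=22 and reports "61% (11/18) of participants no longer met Rome IV criteria". That denominator belongs to a questionnaire outcome. It does not count missed blood or HRV visits, and least of all people who answer questionnaires yet skip the visit. The postintervention assessment is itself in person, so a missed visit may well lose the questionnaire too, which favours the smaller figures.

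A reader might also infer that bias is to be expected, or that choosing mechanisms rests on this number. Nothing in the article suggests arm-dependent loss. The change-score mediation model uses one set of people and is unaffected, and the article calls the analyses exploratory and does not anticipate significant mediation.

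Finally, under random loss the added noise is modest beside the estimator's own. At 20% missing in the second set-up, the listed difference had an SD of 0.172 with mismatched sets and 0.159 on the same people. That is fair, and it limits the importance of the point.

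**Conclusion.** The point holds in a limited form. For HRV, RNA and serum markers, and without imputation, the stated subtraction compares different participants, so the difference does not purely show an indirect effect. At N=50 and an assumed 10-20% without a change score, the sample component under random loss has an SD of roughly 0.04-0.06 outcome SD if the postintervention questionnaire is lost as well, and up to about 0.12 if it is kept. It is centred on zero. A systematic shift of roughly 0.03-0.08 SD, or more under other assumed correlations, requires loss that relates to outcome differently by arm. With no missed visits the component vanishes.

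The 81% is arithmetically right for n=50; what goes unsaid is that it needs a change score from all 50. The loss rates and correlations used here are assumptions, not figures from the article. The consequence is confined to the ranking of exploratory mechanisms.

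**What to change.** In the Statistical Analysis Plan section, state that for each mechanism both mixed models are fitted to the participants with baseline and postintervention values of that mechanism, and that the difference is taken on that set. Use the same baseline constraint in both models and enter the mechanism terms by time; otherwise a common set alone leaves an estimate that cannot reflect mediation. Describe this analysis as being on that set rather than on all randomized participants, with imputation of the mechanism as a sensitivity analysis.

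In Power and Sample Size, state that 81% assumes a change score from all 50, and give the figures for an assumed loss (about 77% at n=45 and 72% at n=40).

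The cost is a few sentences and one refit of the clinical model per mechanism. The unadjusted effect in the mediation table will differ slightly from the main clinical analysis, which needs a footnote, and the quoted power is lower. With 20 participants enrolled as of July 2026 and completion expected in August 2028, there is time to settle this before analysis.

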
## Results

Prior to participant enrollment, IRB approval was obtained and the trial was prospectively registered at ClinicalTrials.gov (NCT06866106) in March 2025. Funding was awarded in June 2025, and following a study start-up period, recruitment commenced in October 2025. As of July 2026, 20 participants have enrolled in the study. Study completion is anticipated in August 2028; at that time, findings related to feasibility, acceptability, and preliminary clinical and mechanistic outcomes will be reported.

## Discussion

### Anticipated Findings

The WISH 2.0 RCT will evaluate the feasibility, acceptability, and preliminary effects of a novel, iteratively refined, phone-delivered PP intervention for IBS and will explore candidate gut-brain mechanisms that might underlie its potential effects. This intervention extends existing BGBTs by explicitly targeting PP well-being, an underexplored yet important contributor to IBS symptom burden, mental health, and health-related quality of life [14,50].

There are several strengths to the WISH 2.0 clinical trial. These include a systematic, evidence-based approach to behavioral intervention and BGBT development; a randomized design with an active and clinically meaningful time- and attention-matched control condition; masking of participants to hypotheses and assessors to treatment condition; processes to ensure intervention fidelity; a priori specified outcomes and use of validated measures; and the exploratory integration of multimodal mechanistic assessments spanning autonomic function, self-reported interoception, gene expression, and immune activation. Exploration of candidate mechanisms early in behavioral intervention development is key to facilitating more focused mechanistic examinations in future larger trials. In addition, the remote delivery format and relative ease of administration (eg, potential delivery by bachelor’s-level interventionists [44,46]) enhance scalability and accessibility, which may facilitate future implementation in real-world clinical settings.

There are also limitations to this study. As a single-site pilot trial with a relatively small sample size, it is not powered to detect statistically significant differences in clinical outcomes or candidate mechanisms; accordingly, analyses of effects and mechanisms will be exploratory. Additionally, although the educational control condition is designed to match time, attention, and credibility, nonspecific factors may still influence outcomes.

If WISH 2.0 is found to be feasible and acceptable and demonstrates promising signals of benefit, these findings will inform the design of a fully powered RCT. In addition, exploratory mechanistic findings may help identify candidate pathways through which PP interventions might influence IBS symptoms, supporting further refinement, optimization, and mechanistic targeting of BGBTs for the IBS population.

### Conclusions

This RCT will provide critical data regarding the feasibility and acceptability of WISH 2.0, a novel PP intervention for IBS. Comparative findings between WISH 2.0 and an educational control condition—including the possibility of equivalent effects—will offer important insights into BGBT mechanisms. These results have the potential to support the refinement and development of scalable, mechanistically targeted BGBTs for IBS and to inform the design of future large-scale trials.
